#### Feasibility and acceptability of the app

We will compute the refusal rates and detail the reasons for failed mobile app installation by consented HCPs in the intervention arm. Qualitative data on the acceptability and barriers/facilitators of using the mobile app by HCPs will be analysed using thematic analysis by employing NVivo V.10 software.

#### Cost and cost-effectiveness

We will estimate unit *setup* and *running costs* for both the introduction of Med Safety in addition to existing PV methods and the use of existing PV methods alone. Costs per ADR report submitted to NPC will be computed (overall; per study arm; per ADR attribute, eg, seriousness, avoidability, causality, etc). We will estimate cost-effectiveness of introducing Med Safety by calculating the incremental cost-effectiveness ratio, which is the cost per additional ADR report submitted to NPC.

### Monitoring

#### Monitoring and evaluation mechanism

The research team will monitor the project’s performance based on the research activities and report progress to the Project Steering Committee, which will sit (online) every 6 months. During monitoring, the research team will continually collect and analyse information on the project’s ongoing research activities. The steering committee will provide independent external evaluation of the project based on the 6 monthly reports from the research team.

#### Stopping rules

A Data Safety Monitoring Board is in place. Midterm interim analysis will be conducted at p<0.01 to assess if the app is substantially better than a priori estimates. The study will otherwise stop when all 382 cART sites have been enrolled and followed up for 30 months. A protocol for patient care is in place at each cART site to evaluate and manage PLHIV who develop suspected ADRs linked to cART and IPT.

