#### Comparison arm

HCPs at the comparison cART sites will be trained and encouraged to use traditional methods of ADR reporting (paper form and web form). All aspects of the training will be identical to those in the intervention arm except that Med Safety will not be introduced to HCPs in the comparison arm. Reminder WhatsApp and SMS about the paper form and web form will be sent out monthly for up to 6 months.

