#### Participant timeline

There are 15 regional referral hospitals each with a catchment of ~25 cART sites. Each team of three research assistants requires 4 weeks to enrol HCPs in one regional catchment. Follow-up at each cART site begins after its enrolment and lasts 30 months. The 30-month follow-up period is considered adequate to monitor durability of the real-life impact of the app on ADR reporting. Four additional months will be required to wrap-up the study, thus, 36 months overall (table 1).

**Table 1 T1:** Schedule of enrolment, interventions and assessments

	Study period						
	Baseline	Follow-up schedule					Close-out
Procedures	(t_0_)	t_0_+3 months	t_0_+6 months	t_0_+12 months	t_0_+15 months	t_0_+30 months	t_0_+36 months

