**Assessments**							
Quantitative survey	x			x			
Mobile app data	x	x	x	x	x	x	
Economic cost data	x	x	x	x			
Interim data analysis					x		
Qualitative study	x			x			
Endline data analysis							x

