#### Sample size

To estimate the number of cART sites required per arm for an effect size of 25%,^26^ we assume power of 80% at the 95% confidence level, mean of 1.0 IPT-linked ADR/month/100 000 treated PLHIV (0.00001) and SD of 1.179 IPT-linked ADRs/month/100 000 treated PLHIV (0.00001179) (SD was computed based on the monthly IPT-linked ADR reports submitted to NPC for 1 year from October 2018 to September 2019), cluster size of 10 HCPs and coefficient of variation of 0.25,^26^ which yields ~114 cART sites per trial arm or 228 in both study arms. A minimum of 189 cART sites per arm or 378 in both study arms (66% increment) will be required to cater for the following limitations: (1) the large proportion of HCPs who do not own smartphones of ~50%–60% as previously estimated^21 22^ – and is 26% (95% CI of 23% to 30%) from limited rollout of RCT; (2) refusal to participate by eligible HCPs of ~5% as previously estimated^27^ – and is 0% (95% CI of 0% to 2%) from limited rollout of RCT; (3) loss to follow-up due to the relatively long follow-up period of 30 months (~10%); and (4) contamination due to information sharing between study arms through social media (~30%).^28^ We shall enrol 382 cART sites (191 per study arm) to cater for other unforeseen limitations; thus, recruiting up to 3820 HCPs (1910 HCPs per trial arm). Limited rollout of the RCT suggests a cluster size of 7.2 (629/87) HCPs. We shall retain the average cluster size of 10 HCPs because the RCT has not yet enrolled from the central region of Uganda (with the country’s capital city) where cART sites tend to be much larger with more HCPs per site than the more rural eastern, western and northern regions.

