#### Effectiveness

Descriptive data will be aggregated to obtain the number of HCP-reported ADRs per 100 000 treated PLHIV per trial arm and compared at cluster level using the Student’s t-test or Wilcoxon rank-sum test, as appropriate, to determine if the app significantly increases ADR reporting. We will assess if the introduction of Med Safety increases the rate of ADR reporting by HCPs to NPC versus the use of existing PV methods (paper and online) alone during 30 months of follow-up and effect size of 25% at 5% level of statistical significance and power of 80%.

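### The month-15 interim look at p<0.01 is not deducted from the 5% given to the 30-month test, and neither its null hypothesis nor the consequence of crossing it is stated

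*Protocol article*

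**What the plan says.** Stopping rules: a "Midterm interim analysis will be conducted at p<0.01 to assess if the app is substantially better than a priori estimates". The next sentence but one of substance is that "The study will otherwise stop when all 382 cART sites have been enrolled and followed up for 30 months". The heading and the word 'otherwise' together imply that a positive interim result can end the trial, although the protocol does not say so outright.

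Table 1 marks the row "Interim data analysis" in the column for 15 months after baseline.

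Effectiveness: the arms are compared at cluster level by t-test or rank-sum test over 30 months of follow-up, with "effect size of 25% at 5% level of statistical significance and power of 80" per cent. Sample size: "we assume power of 80% at the 95% confidence level". Neither section lowers the final level or mentions the interim look.

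Participant timeline: the 30-month period is "considered adequate to monitor durability of the real-life impact of the app on ADR reporting". In the comparison arm, reminders "will be sent out monthly for up to 6 months"; the intervention arm has the same limit.

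**The concern.** Two chances to declare the app effective, one at 0.01 and one at 0.05, give a total false-positive risk above 0.05 unless one threshold is tightened. The document states both thresholds and does not link them.

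There is also a tension over purpose. The trial is given 30 months so that durability can be observed, yet the same document allows it to end at half that time. A trial stopped because an interim estimate was high also tends to report too large an effect.

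**Working it through.** **1. The plan's own figure, to see what level it uses.** Inputs from Sample size: "mean of 1.0 IPT-linked ADR/month" per 100 000, a 25% effect (difference 0.25), SD 1.179, 10 professionals per cluster, clustering parameter 0.25.

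- Individuals per arm = 2 × (1.960 + 0.842)² × 1.179² / 0.25² = 349.1, so 350.
- Design effect = 1 + (10 − 1) × 0.25 = 3.25.
- Clusters per arm = 350 × 3.25 / 10 = 113.75, so 114, as stated. The 66% increment gives 114 × 1.66 = 189, also as stated.

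This match treats 0.25 as an intracluster correlation. Used as the coefficient of variation it is labelled to be, it gives 57 per arm, or 114 in both arms together. Either way, the whole two-sided 5% is spent on one test.

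**2. Overall error if the interim tests no difference.** Let Z₁ and Z₂ be the interim and final statistics, bivariate normal with correlation √t, where t is the information fraction. The overall error is

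1 − P(|Z₁| < 2.576 and |Z₂| < 1.960).

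The protocol does not give t. By follow-up time it is 15/30 = 0.5. It would be lower if month 15 is counted from the start of staggered enrolment, and could be higher if stable between-site differences dominate the variance. Hence a range:

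| t | Overall error, 0.01 then 0.05 | Final level that keeps 5% | Overall error, 0.001 then 0.05 |
|---|---|---|---|
| 0.2 | 5.77% | 0.0421 | 5.07% |
| 0.4 | 5.57% | 0.0441 | 5.04% |
| 0.5 | 5.46% | 0.0452 | 5.02% |
| 0.6 | 5.34% | 0.0464 | 5.01% |
| 0.8 | 5.11% | 0.0489 | 5.00% |

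A simulation of 10 million trials at t = 0.5 gave 5.45%. The ceiling for any t is 0.01 + 0.05 = 6%.

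**3. Other readings, at t = 0.5.**

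- Only a result favouring the app can stop the trial: 5.23% overall, or 2.73% against a nominal 2.5% in the app's favour.
- Both looks one-sided (0.01, then 0.05): 5.38%.
- Interim tested against the assumed 25% increase: under the design assumptions the expected interim Z is 2.802 × √0.5 = 1.981, so the no-difference statistic would have to exceed 2.576 + 1.981 = 4.557. With no true effect this has a chance of about 0.0003%, and the overall error is 5.00%.

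**4. Could the trial stop at month 15?** Take a true 25% effect, 80% power and t = 0.5. The chance of crossing p<0.01 in the app's favour is 1 − Φ(2.576 − 1.981) = 1 − Φ(0.595), about 28%. Crossing needs an observed increase of 25% × 2.576/1.981, about 33%. Given crossing, the mean of Z₁ is 1.981 + φ(0.595)/0.276 = 1.981 + 1.21 = 3.19, which is 1.6 times its expected value. A true 25% increase would then be reported as about 40% on average.

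**5. Reminders and durability.** Six months of reminders cover 6/15 = 40% of the follow-up at month 15 and 6/30 = 20% at month 30. Time after the reminders end is 9 months and 24 months respectively.

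**The case against.** **The interim null is not stated.** The stated purpose is to see whether the app beats prior estimates, and the prior estimate is a 25% increase. Read literally, the p<0.01 test could be against 25%, and then there is no inflation. This stands as a real ambiguity and limits the confidence of the point. Against it, the only test the protocol defines is arm against arm, and under that test p<0.01 at t = 0.5 already needs an observed increase of about 33%. The phrase therefore also fits the ordinary null.

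**The 5% may be an overall level.** A statistical analysis plan or board charter that is not shown might divide it between the looks. That is possible. However, this document attaches 5% to the 30-month comparison and sizes the trial on it, so the link should be stated here.

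**The excess is small.** It is about half a percentage point at t = 0.5 and would rarely change a conclusion. This stands in full.

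**A reader might infer that an early stop would report a reminder-driven effect.** The documents do not support that. Reminders go to both arms for the same period, so their larger share of a 15-month dataset does not by itself bias the contrast between arms, and about 9 reminder-free months would be in hand. Durability is given as the reason for the follow-up length; it is not a listed objective or outcome.

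**A reader might also infer that follow-up must continue after crossing.** That is a design choice with its own trade-offs, not the correction of an error.

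**Conclusion.** The point holds in a limited form. On the reading that the interim tests no difference, with two-sided tests and half the information at month 15, the overall type I error is about 5.5% rather than 5%. It is 5.8% to 5.1% for information fractions of 0.2 to 0.8 and at most 6%. If the interim tests against a 25% increase, the error stays at 5%. It would therefore go too far to say flatly that the 5% level is broken: the document leaves open which case applies.

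Separately, the stopping rule and the reason given for 30 months need to be reconciled. Under the design assumptions a crossing at month 15 has a chance of about 28%, and it would tend to overstate the effect. Severity is minor; confidence is moderate.

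**What to change.** 1. State that the interim tests the hypothesis of no difference between arms, and whether it is one- or two-sided.
2. Then choose one of two options:
   - Keep the interim at 0.01 and set the final level to about 0.045, recomputed at the actual information fraction. At t = 0.5 the level is 0.0452 (|z| > 2.003). Power over both looks is about 79.2% instead of 80% (78.8% for the final test alone). In the plan's own formula this is 117 clusters per arm instead of 114, and 117 × 1.66 = 194 after the increment, against 191 enrolled.
   - Set the interim boundary at p<0.001 and keep the final test at 5%, for an overall 5.02% at t = 0.5. The price is a harder early stop: under the design assumptions the chance of crossing falls from about 28% to 1 − Φ(3.291 − 1.981), about 9.5%.
3. State under Stopping rules whether crossing the boundary ends follow-up. If it does, say how the durability rationale in Participant timeline will be met, and that the early estimate is likely to be too high.

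This takes a few sentences in the protocol or the monitoring board's rules, agreed before the interim look. It needs no new data.

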### Ethics and dissemination

We obtained ethical approval for the study from the School of Biomedical Sciences Research and Ethics Committee at Makerere University College of Health Sciences (SBS-REC-720), and subsequently undertook research registration with the Uganda National Council for Science and Technology (HS1366ES). Administrative clearance is being obtained from participating cART sites and written informed consent sought from participating HCPs (online supplemental file 3).

10.1136/bmjopen-2022-061725.supp3Supplementary data

### Dissemination strategies

During the study, limited communication tailored specifically for each study arm will be made by the study team to limit the effect of contamination.

#### Engaging healthcare providers

We shall employ video conferencing, webinars and face-to-face engagements to deliver continuing professional education sessions to HCPs on ADR risk assessments for PLHIV prior to the initiation of DTG regimens and IPT and the detection, management and reporting of ADRs for PLHIV already receiving DTG/IPT. Video conferencing is preferred to minimise the spread of COVID-19. If virtual meetings are not feasible, then face-to-face meetings will be held in full observance of the Ministry of Health’s guidelines for limiting the spread of COVID-19: social distancing, use of face masks and handwashing, especially for regional trainings of HCPs in remote areas where the internet might not be accessible and during the enrolment of study sites. The NPC in concert with Ministry of Health developed PV training materials for active drug safety monitoring and management of ADRs to DTG/IPT. We shall adapt and update these materials with the results of our study for academic training and also tailor them for healthcare service delivery trainings to be conducted nationwide in partnership with NPC and Ministry of Health.

#### Reaching healthcare providers, policymakers and drug regulators

This work underpins the wider rollout of Med Safety to improve PV across Uganda and beyond. This study is being implemented in direct partnership with cART sites, Uganda’s NDA, which is the PV coordinating body in Uganda, UK’s MHRA and WHO. Therefore, the study results will be readily available for immediate use to inform policy and practice by these key stakeholders. The NDA and MHRA (the software developers) will identify the barriers to the app’s implementation and mitigate them as well as the facilitators and exploit them. Uganda’s experience could be exploited to scale up the app in other low-income and middle-income countries.

#### Reaching researchers

In addition to social media and webinars, as mentioned previously, we aim to reach researchers through traditional methods. We shall present our work at conferences including: Joint Annual Scientific Health Conference, Makerere University College of Health Sciences; International Society of Pharmacovigilance Annual Meeting; Conference on Retroviruses and Opportunistic Infections; International AIDS Society Conference, Royal Society of Tropical Medicine and Hygiene Annual Meeting, among others. We expect to produce at least six open access publications from this work by the end of this study. We shall target journals including: Lancet Global Health; Drug Safety; Pharmacoepidemiology and Drug Safety, Journal of the International AIDS Society; Journal of Antimicrobial Chemotherapy; and Journal of Acquired Immune Deficiency Syndromes, etc.

### Project impact

Improving the reporting of suspected ADRs via digital PV is the first step towards boosting the volume of safety data available for robust signal detection analyses, improving understanding of the risk profiles of medicines and preventing future occurrence of avoidable ADRs. Improved PV translates into better recognition of serious ADRs and, ultimately, safer patient care. This work underpins future proposals to understand the risk factors for ADRs in PLHIV.

### Protocol amendments

Protocol modifications that may impact on implementation of the study and affect patient safety including changes of study objectives, study design, study population, sample sizes, study procedures or significant administrative aspects will require a formal protocol amendment. Such amendment will be agreed on by the study investigators and approved by the School of Biomedical Sciences Research & Ethics Committee prior to implementation.

### Patient and public involvement

Patients were not involved in designing this study and will not be directly involved in the conduct, reporting and dissemination of the research. However, HCPs were involved in refining the study tools and will participate in conducting, reporting and disseminating the research.
